### Visit 2 - 4-week follow-up

*At 4 weeks after randomisation*, participants will be contacted via telephone in order to assess smoking status, numbers of quit attempts lasting more than 24 hours, quality of life information (EQ-5D) and use of NHS and non-NHS smoking cessation support in the period since randomisation. This visit will, in general, be performed via telephone by a member of the study team at the co-ordinating centre, blind to treatment allocation; however, should the study team be unable to contact by the participant by telephone, other methods will be used in an attempt to elicit the best response. These include; posting a short questionnaire with explanatory letter and pre-paid return envelope, or sending a link, which allows web-based completion or by text.

It is possible that if members of the co-ordinating centre study team speak to participants at the 4-week follow-up, they may become un-blinded for the late pregnancy follow-up (visit 3). However, the value of exploring the feasibility of different follow-up approaches for this pilot trial outweighs the small risk of bias presented by this scenario.

### Visit 3 - late pregnancy/postnatal follow-up

*At 36 weeks gestation*: Participants will be asked to complete a questionnaire (data to be collected up to 10 weeks after estimated delivery date will be acceptable for use). This will include quality of life information (EQ-5D) and measures of smoking behaviour, attitudinal/behavioural information, use of NHS smoking cessation support and participants’ ratings of the intervention (MiQuit arm only). As for the 4-week visit, this visit will be performed mainly via telephone by a member of the study team at the co-ordinating centre, blind to treatment allocation. As for the 4-week visit, previously-described alternative methods will be employed to elicit the best response rate.

It is recognised that asking about the intervention at follow-up will result in the researcher who conducts the late pregnancy follow-up becoming un-blinded. To ensure that this has minimal impact on follow-up data obtained, the participants will be asked items about the intervention at the end of the interview/questionnaire starting with the question ‘*Did you receive any stop smoking text messages from the study team*?’

### Visit 4 - validation of smoking status

During this assessment, whether in person or by post, participants will be asked to report their smoking status and recent use of nicotine replacement therapies.

Participants self-reporting abstinence in late pregnancy will have their smoking status validated by exhaled carbon monoxide (CO) readings and/or salivary cotinine samples. The validation of smoking cessation would be initiated as soon as possible after notification of abstinence at visit 3.

Exhaled CO will be measured using a validated hand held CO monitor and can only be taken when a researcher is able to visit the participant in their home. Saliva samples for cotinine (a metabolite of nicotine) analysis could be collected at the same visit. Ideally both forms of assessment would be used, but either CO or cotinine assessment would be sufficient on their own if difficulties in getting a valid sample are experienced with either method. Where it is not possible to visit a participant in their home, a salivary sample pack will be sent by post and participants will be invited to return a sample in a pre-paid postal packet. Written consent agreeing to provide the samples for validation will be obtained from any participants who did not give this consent at baseline (that is, those who were recruited via telephone). This consent will be obtained either during the home visit or by sending a consent form for the participant to complete and return with a postal saliva sample. Cut-off points for biochemical verification will be determined according to the latest evidence, but defined abstinence is likely to be in the region of <9 ppm for CO readings and <10 ng/ml for salivary cotinine [17].

### Duration of the trial

It is anticipated that the total duration of the study will be 20 months. This will include 12 months of recruitment and 8 months of follow-up.

Late pregnancy outcome ascertainment is intended to be at 36 weeks gestation, or at latest, within two weeks of birth. However, if outcome data become available after this point, we will permit it to be used in analyses provided the timing of data collection is no later than 10 weeks after the estimated due date.

Qualitative interviews undertaken as part of a process evaluation will be carried out shortly after the late pregnancy follow-up and are not planned to be carried out any later than 10 weeks after the estimated delivery date.

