### Feasibility outcomes

Feasibility outcomes include the following:Recruitment rate of participants from pregnant smokers attending trial centres.For individual trial groups, proportions of participants with validated smoking cessation data collected between 4 weeks after randomisation until late pregnancy (at approximately 36 weeks gestation).For both trial groups combined, collection of validated smoking cessation data, as above, measured in late pregnancy (approximately 36 weeks gestation).

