### Smoking outcomes

Smoking outcomes are described below:Proportion of participants with self-reported, continuous abstinence from smoking from 4 weeks after randomisation until follow-up in late pregnancy (approximately 36 weeks gestation), *validated* by exhaled CO and/or saliva cotinine estimation; there will be no ‘grace period’ [12]. Participants who report smoking no more than five cigarettes in total between the start of their quit attempt (within 4 weeks of randomisation) and late pregnancy will be considered to have quit smoking [13].(Note: Participants who cannot be contacted at 4 weeks after randomisation, but who, in late pregnancy, report cessation as outlined above, will be counted as positive for the late pregnancy cessation outcome).NB: We anticipate the above outcome being a *primary outcome* for any definitive trial that follows this study.Proportion of participants with self-reported abstinence from smoking from 4 weeks after randomisation until late pregnancy (at approximately 36 weeks gestation).Proportion of participants with self-reported and validated 7 day point prevalence cessation measured in late pregnancy (approximately 36 weeks gestation).Proportion of participants with self-reported 7-day point-prevalence cessation at 4 weeks after randomisation.Number of 24 hour quit attempts reported in late pregnancy (approximately 36 weeks gestation).

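### Outcomes collected up to 10 weeks after the due date are pooled with 36-week data, so the ascertainment rate alone cannot show that smoking status was obtained in late pregnancy

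*Protocol article*

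**What the plan says.** Under Duration of the trial, the protocol article gives a target and an outer limit: "Late pregnancy outcome ascertainment is intended to be at 36 weeks gestation, or at latest, within two weeks of birth". The next sentence relaxes that limit: "if outcome data become available after this point, we will permit it to be used in analyses provided the timing of data collection" does not run past a second cut-off, set 10 weeks beyond the due date. The Visit 3 section repeats the allowance, stating that "data to be collected up to 10 weeks after estimated delivery date will be acceptable for use", and its title is "Visit 3 - late pregnancy/postnatal follow-up".

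The outcomes themselves are tied to late pregnancy. Feasibility outcomes counts, for each group, "proportions of participants with validated smoking cessation data collected between 4 weeks after randomisation until late pregnancy (at approximately 36 weeks gestation"). Smoking outcomes defines the anticipated primary outcome of a definitive trial as "continuous abstinence from smoking from 4 weeks after randomisation until follow-up in late pregnancy (approximately 36 weeks gestation"), and another outcome as "self-reported and validated 7 day point prevalence cessation measured in late pregnancy (approximately 36 weeks gestation").

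Three further provisions matter. Visit 4 starts biochemical validation only after a woman reports abstinence at Visit 3. The sections on missing data and on the intention-to-treat population count missing smoking status as smoking. The Discussion says that high ascertainment would mean the piloted outcome could serve a definitive trial to measure and validate cessation across the whole of pregnancy.

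**The concern.** This is a pilot, and its primary objective is to estimate planning parameters. Two of these are the ascertainment of validated smoking status by group and the combined quit rate at 36 weeks. The article sets a limit of two weeks after birth and then overrides it, so both parameters pool data from the intended window with data collected weeks after delivery. This is a stated inclusion rule, not a detail left for the analysis plan.

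Two things are at stake. First, a single ascertainment figure for the wider window does not show how often status was obtained at or near the intended time, which is what the Discussion's argument needs. Second, breath CO, salivary cotinine and any 7-day report tied to the day of contact describe smoking after birth when the contact is late. The article does not say where the abstinence period ends for a woman first reached after birth.

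**Working it through.** **Stated precision.** The article gives half widths of 95% intervals for cessation proportions of about 10%.
- Per group: 1.96 × √(0.10 × 0.90 / 200) = 0.0416, against a stated 4%.
- Combined: 1.96 × √(0.10 × 0.90 / 400) = 0.0294, against a stated 3%.

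Both reproduce. They describe sampling error only and say nothing about when outcomes were collected.

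**Length of the window.** Take the due date as 40 weeks (assumed). The last acceptable date is 40 + 10 − 36 = 14 weeks after the target. The first part of that span is already inside the intended window. For a birth on the due date, the part beyond the article's own limit is 10 − 2 = 8 weeks.

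**Ascertainment.** Let N be the number randomised, I the number with outcome data by two weeks after birth, and L the number first obtained later.
- Intended window: I / N
- Extended window: (I + L) / N
- Difference: L / N, which is never negative

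The direction is certain. The size is not, because the documents give neither I nor L. As an illustration only, assume 80% are ascertained by 10 weeks after the due date and a share s of those outcomes is late. The intended-window rate is then 80% × (1 − s).

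| Assumed late share s | Intended window | Gap (points) |
|---|---|---|
| 5% | 76% | 4 |
| 10% | 72% | 8 |
| 20% | 64% | 16 |
| 30% | 56% | 24 |

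**Classification of women first reached late.** The table compares using their data with refusing them under the missing-equals-smoking rule.

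| Late pregnancy | At late contact | Data used | Data refused |
|---|---|---|---|
| Abstinent | Abstinent | Quit, if validated | Smoking |
| Abstinent | Relapsed | Smoking on validated outcomes | Smoking |
| Smoking | Stopped after birth | Could be quit on the 7-day outcome | Smoking |
| Smoking | Smoking | Smoking | Smoking |

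Three results follow.
- In the intention-to-treat analysis, no row moves from quit to smoking when late data are used. The extended window can add quitters but no failures, so restricting it can only lower that quit rate or leave it unchanged.
- Row 2 is an error against true late-pregnancy status. It also enters the complete-case analysis as a failure, where refusing the data would have removed the woman from the denominator.
- Row 3 is the opposite error. It arises if the seven days are counted back from the contact date.

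The net direction of misclassification is therefore not established.

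**The case against.** The window is fixed in advance, stated in two places and visible in the title of Visit 3. The outcome being piloted is the one the article expects a definitive trial to use, and a trial keeping the same window would obtain the same ascertainment rate. A full analysis plan is promised and may already tabulate outcomes by timing. All of this stands, so a reader who infers that ascertainment is simply inflated goes too far: it is higher only relative to the article's own two-week limit, by an unknown amount. Disclosing the window does not separate the data, however, and the Discussion's claim concerns cessation through pregnancy.

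A reader might also infer that relapse after birth is scored as failure in pregnancy, so that the primary quit rate looks worse. The documents do not support this. No rule says so: the abstinence definition and the five-cigarette allowance both end at late pregnancy. The effect arises only through the timing of validation and the unclear end of the period for late contacts. Under missing-equals-smoking, a woman who relapsed after birth counts as smoking whether her late data are used or refused. Understatement holds only against true 36-week status or in the complete-case analysis.

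**Conclusion.** The point holds in limited form and is worth acting on before analysis. The article sets a limit of two weeks after birth, then admits data to 10 weeks after the due date under the same label. The resulting ascertainment rate cannot be lower than that of the intended window. Unless it is split, it cannot by itself support the Discussion's claim that cessation through pregnancy can be measured and validated.

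The excess is L / N and cannot be computed from the documents. The gap of 4 to 24 points shown above rests wholly on the assumed 80% ascertainment and 5 to 30% late share. No net bias in the quit rate is shown, and none between arms. What is established is that late contacts can be misclassified in either direction relative to late-pregnancy status.

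**What to change.** Keep the extended window for the intention-to-treat analysis, and make these changes:
- Report ascertainment by arm, and quit rates by arm and combined, at two cut-offs: data collected by two weeks after birth, and data collected to 10 weeks after the due date.
- Give the number of later outcomes in each arm.
- Add a sensitivity analysis of the smoking outcomes by collection window. For validated outcomes, classify by the date of the sample as well as the report.
- For women first reached after birth, end the self-reported abstinence period at delivery, and say so in the outcome definition.

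The cost is a small amount of extra analysis. Table 1 already records visit dates at Visits 3 and 4. The date of birth is also needed for the split. The visible downside is a less favourable ascertainment figure for the intended window, but that is the figure needed to judge whether status can be obtained in late pregnancy.

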### End of the trial

The end of the trial will be when the late pregnancy outcome has been ascertained for the final participant or it is too long after this participant’s estimated delivery date (EDD) for such information, if collected, to be used.

### Participant stipends and payments

All participants will receive compensation for their time to the value of £5 for each study visit in the form of a national high street shopping voucher. Those participants who are asked to provide a saliva sample will be sent a £5 voucher with the sample request pack and a second £5 voucher on receipt of a saliva sample. Those participants who participate in a longer in-depth qualitative interview to gain information on their experience of the intervention (MiQuit arm only) will receive £20 in vouchers as compensation for their time.

### Qualitative interviews for process evaluation

A small number of semi-structured telephone interviews will be carried out with a selection of participants from the MiQuit arm in order to address secondary objective 4. This process evaluation will provide important data on participant’s experience of receiving support from MiQuit within the context of their everyday lives and participation in a trial. Semi-structured interviews will enable the researcher to have some control over the data collected to compliment the trial evaluation but at the same time be interactive and allow the participant control also. The findings will greatly assist the design of a definitive trial and optimisation of the intervention.

Participants will be purposively selected according to smoking status and cessation behaviour and use of the MiQuit system, including those who decide to discontinue use of MiQuit. Only participants who have already consented at baseline to be contacted to discuss participation in an interview will be contacted and will receive additional information before the call on what to expect. After completing the late pregnancy follow-up, participants in the MiQuit arm, who indicated at baseline that they were happy to be contacted about participation in an interview, will be sent a specific information sheet and blank consent form. A researcher will call a number of participants (not all) and establish if the participant is still interested in going ahead with the interview. If they are happy to continue, the researcher will request verbal consent for the interview and proceed with the interview. If the participant is interested but unable to continue with the interview at that time, a specific date will be set for the interview to take place. In every case, verbal consent will be recorded by the researcher before the interview goes ahead, and a copy of the consent form will be sent to the participant. The participant will be made aware that the interview will be audio-recorded and that they can withdraw from the interview at any time and that this would not affect their subsequent care or rights. Participants will be recruited until the researchers feel that data saturation has occurred (that is, the point where few novel insights are generated from the most recent interviews). Given the focused nature of the interviews, it is anticipated that this would be reached after interviewing 10 to 15 participants. The interview schedule will include questions on the participants’ general experience of smoking and quitting during pregnancy, their experience of using and interacting with MiQuit, their feelings towards whether and how MiQuit might have helped them engage or maintain a quit attempt, and their thoughts on how it could be improved.

The interviews will be undertaken by experienced personnel and last up to 60 minutes. The interviews will be analysed using framework analysis, assisted by the qualitative analysis software NVivo. This will include looking at two main characteristics of the participants: that is, smoking status and use of system including those who discontinue (text STOP) and how these relate to several aspects of the experience of receiving the intervention including factors that may affect interaction with MiQuit, feelings towards message content and system features and suggestions for improvements for future use.

A number of semi-structured telephone or face to face interviews will also be carried out with a selection of recruiting site research staff involved in the study in order to address secondary objective 5. This will provide important data on the staff experience of running and recruiting into the MiQuit study. As for the participant interviews, the semi-structured interviews will enable the team to have some control over the data collected to complement the trial evaluation but also be interactive to allow the local site research staff to have some control too. The findings will greatly assist the practical design of a definitive trial.

A number of staff from recruiting centres will be selected for interview, to allow a variety of opinions and comments to be collected.

The objectives for these interviews are as follows:To develop a taxonomy for describing MiQuit trial recruitment processes.To describe research midwives’ perceptions of the key facilitators for and barriers against recruitment.To relate key facilitators and barriers to recruitment processes and so further understanding of how, in a definitive trial, recruitment could be maximised.To describe from the perspective of research midwives, those factors, which are perceived to influence acute trusts’ decisions to act as a trial centres (NB: after analysis, we will be in a position to hypothesise about how best to encourage trusts to sign up to being trial centres in a definitive study).

Issues to be covered in staff interviews will include the following:The particular process they used in their site to identify, engage and enrol participants, including the consent process;their views on the local trial processes, including why particular processes were used, what worked well or was challenging, what the study team could have done to make this easier, particularly focussing on issues that it is possible to influence;how decisions are made about Trust involvement in a particular trial and what influenced them to take part, whether they would consider being involved in a similar study again, insights into best way to achieve meaningful collaboration; andtheir views on the intervention.

The interviews will be audiotaped and analysed using thematic qualitative analysis.

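### MiQuit-only interview contact starts from visit 3, the same event that starts biochemical validation, and nothing makes it wait for the sample (minor)

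*Protocol article*

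**What the plan says.** **Sequence of visits.** The Adherence section and Table 1 identify the late pregnancy/postnatal follow-up as visit 3. Validation by CO and/or saliva cotinine is a separate visit 4.

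**Interview contact, MiQuit arm only.** The section on qualitative interviews says: "After completing the late pregnancy follow-up, participants in the MiQuit arm, who indicated at baseline that they were happy to be contacted" about an interview "will be sent a specific information sheet and blank consent form". A researcher then telephones some of them. On numbers, "it is anticipated that this would be reached after interviewing 10 to 15 participants". On selection, "Participants will be purposively selected according to smoking status and cessation behaviour and use of the MiQuit system". Interviews last up to 60 minutes, and interviewees "will receive £20 in vouchers as compensation for their time" (Participant stipends and payments). Under Duration of the trial, interviews are to be "carried out shortly after the late pregnancy follow-up" and no later than 10 weeks after the estimated delivery date.

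**Validation, both arms.** "The validation of smoking cessation would be initiated as soon as possible after notification of abstinence at visit 3". It takes a home visit or a posted kit, plus written consent from women who enrolled by telephone. Visit 4 also asks again about smoking status. Outcome data are usable up to 10 weeks after the due date, the same outer limit as for interviews.

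**Outcome.** The efficacy measure is prolonged abstinence that has been biochemically validated (Assessment of efficacy). Missing smoking status counts as smoking (Procedures for missing, unused and spurious data).

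**The concern.** Completing visit 3 opens the way to interview contact, and a quit reported at that visit starts sample collection. The first happens in one arm only. Validation takes time to arrange and the interview papers are due in the same period, so some MiQuit women may be mailed, called or interviewed about quitting before their sample is obtained. Selection by smoking status and cessation behaviour makes it likely that reported quitters, the only women asked for samples, are among those interviewed.

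Because the outcome requires a sample, an arm-specific change in sample provision changes that arm's validated quit rate even if true abstinence is equal. Three things would be touched: the per-arm ascertainment of validated cessation, which is a primary objective; the late-pregnancy odds ratio, which feeds the economic modelling; and the outcome that the protocol expects to be primary in a definitive trial.

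The protocol guards against similar problems elsewhere. At visit 3 the questions about the intervention come last, to limit their effect on the follow-up data. The step from visit 3 to visit 4 has no such protection.

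**Working it through.** **1. The plan's own precision.** At a 10% quit rate the 95% half width is 1.96·√(0.10·0.90/n). This gives 4.16 points for n = 200 and 2.94 points for n = 400, which agrees with the stated ±4% and ±3%. The log-odds-ratio interval with 200 per arm, at odds ratio 1.3 and a 10% control rate, is 0.70 to 2.42, as in Table 4. At a 5% control rate it is 0.55 to 3.05, against 0.56 to 3.05 in Table 4 (a rounding difference). This point disputes none of these figures.

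**2. Inputs for the sensitivity calculation.**
- From the protocol: 200 per arm, late-pregnancy control quit rates of 5% and 10% (10 and 20 validated quitters), and 10 to 15 interviews.
- Assumed: no true effect; sample return of 75% among reported quitters, with 60% to 80% as the range; the change in return; and 5 to 8 reported quitters among those interviewed.

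With b validated quitters in control and x in MiQuit, OR = [x/(200 − x)] / [b/(200 − b)].

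**3. Only interviewed quitters affected, return up 20 points.** The extra validated quitters number 5 × 0.20 = 1.0 to 8 × 0.20 = 1.6, or 0.5 to 0.8 points of the arm.
- b = 20: (21/179)/(20/180) = 1.06; (21.6/178.4)/(20/180) = 1.09.
- b = 10: (11/189)/(10/190) = 1.11; (11.6/188.4)/(10/190) = 1.17.

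**4. Upper scenario: all MiQuit reported quitters contacted, return up 10 points.**
- b = 20: reported quitters 20/0.75 = 26.7, extra 2.67; (22.67/177.33)/(20/180) = 1.15.
- b = 10: reported quitters 10/0.75 = 13.3, extra 1.33; (11.33/188.67)/(10/190) = 1.14.

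With 7% to 15% reporting abstinence and control return of 60% to 80%, the odds ratio is 1.07 to 1.09 for +5 points, 1.13 to 1.19 for +10 and 1.27 to 1.38 for +20. The last range needs a contact that is mostly a mailing to raise return by 20 points in every reported quitter.

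**5. The opposite direction.** If the contact is a burden and return falls by the same amounts:
- Step 3 becomes (19/181)/(20/180) = 0.94 and (18.4/181.6)/(20/180) = 0.91 at 10%, and (9/191)/(10/190) = 0.90 and (8.4/191.6)/(10/190) = 0.83 at 5%.
- Step 4 becomes (17.33/182.67)/(20/180) = 0.85 and (8.67/191.33)/(10/190) = 0.86.

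**6. Scale.** With no effect, the standard error of the log odds ratio is √[2(1/20 + 1/180)] = 0.33 at 10% and √[2(1/10 + 1/190)] = 0.46 at 5%. The largest shifts in steps 3 and 4 are ln 1.15 = 0.14 at 10% and ln 1.17 = 0.16 at 5%. These are 0.42 and 0.34 standard errors.

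**The case against.** The case against giving this weight is strong on several counts.

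- **Overlap is permitted, not scheduled.** A reader might infer that interviews take place while samples are still outstanding. No section says so, and validation is meant to begin promptly. What stands is that no section prevents it.
- **Reach is uncertain.** A reader might infer that every MiQuit woman who agreed at baseline is mailed. The interview section can be read that way, but footnote e of Table 1 says only a small number will be contacted. Agreement is optional and its uptake is not given. The scenario with all reported quitters contacted is therefore an upper one.
- **The £20 is not a sample incentive.** It pays for the interview and is expected to reach about 10 to 15 women, some of whom will be smokers who owe no sample. The vouchers for saliva samples (£5 with the pack, £5 on receipt) are the same in both arms.
- **Direction is unknown.** Nothing in the protocol shows that an interview approach raises sample return. A long call could lower it.
- **Other data are protected.** Self-report at visit 3 precedes any interview contact and supports a separate outcome. Per-arm collection of validated data is itself reported, so a marked difference in return could be seen.
- **The pilot has no single primary outcome**, and the protocol says that it is not powered for a precise treatment effect.

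These objections limit the size and certainty of the point. They do not remove it: the contact is confined to one arm, its order relative to the sample is open, and a wide interval does not cancel a systematic difference between arms.

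**Conclusion.** The point holds as a minor weakness of sequencing. The protocol lets interview contact in the MiQuit arm precede the validation sample, with no counterpart in control, and the validated outcome depends on that sample.

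The documents do not support saying that the odds ratio is biased towards MiQuit, since both the direction and the size of any effect on sample provision are assumptions. Under those assumptions the shift is about 1.06 to 1.17 if only interviewed quitters respond (return up 20 points) and about 1.15 in the upper scenario (return up 10 points in all MiQuit reported quitters). A fall in return would give shifts of similar size below 1. All of these are under half a standard error of the planned estimate.

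**What to change.** In Duration of the trial and in the section on qualitative interviews, state that for women reporting a quit at visit 3 the interview mailing and call are made only after the visit 4 sample is obtained, or once a fixed short period has passed since it was requested. Women reporting smoking can be approached at once.

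The period must be short. Waiting until outcome data are no longer usable would not work, because that limit, 10 weeks after the due date, is also the limit for interviews. Women who never return a sample would then be lost to the purposive selection. A sample that arrives after the fixed period could still follow interview contact, so recording both dates would let any remaining overlap be counted.

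The cost is a short delay and slightly poorer recall for a few interviewees. Sample size, visits and stated precision do not change.
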